### Statistical analysis

5.10

All participants will be analyzed in the group to which they were randomly assigned, regardless of their adherence to the intervention or whether they completed the study. For participants who are lost to follow-up, we will use multiple imputation to handle missing outcome data, under the assumption that data are missing at random. This approach minimises bias and preserves the benefits of randomization. Data will be entered using Excel and statistically analysed using SPSS27.0 software. The data of count data were expressed as frequency and rate; the data of measurement data conforming to normal distribution were described as mean ± standard deviation, and those not conforming to normal distribution were expressed as median (M) and quartile (P25, P75). Count data were analysed using the chi-square test to analyse the differences between the two groups. Prior to inter-group comparisons, univariate analyses were conducted: independent samples t-tests or one-way ANOVA were employed for data conforming to a normal distribution, while the Mann–Whitney U test or Kruskal-Wallis H test was utilized for non-normally distributed data. Paired t-test was used for intra-group comparisons, and repeated-measures ANOVA was used to evaluate the trend of changes in each index, with *p* < 0.05 as the test level.

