### Study setting and randomization

2.2

The study remained single-blind, with participants unaware of their group allocation. All outcome assessors, including the triage nurses and laboratory staff, were blinded to the group assignments to minimise measurement bias. Data were collected and analysed by an independent third-party researcher and anonymised and coded to reduce measurement bias. Physiological outcome indicators were assessed at outpatient review by blinded triage nurses and laboratory staff who were unaware of subgroup information. The study population was screened from patients admitted to the inpatient Neurology Department between June and December 2025, following the inclusion and exclusion criteria, and the study will be conducted in the Neurology Department of Linyi Central Hospital, Shandong Province, China, in the first and second wards.

Eligible participants were randomly allocated to either the intervention group or the control group in a 1:1 ratio. The randomization sequence was generated by an independent biostatistician using a computer-based random number generator in SPSS (version 27.0, IBM Corp.). To ensure balance in group sizes over time, block randomization with a fixed block size of 4 was utilized. To control for potential baseline imbalances in key prognostic factors, the randomization was stratified by baseline NIHSS score (≤5 vs. > 5).

Allocation concealment was guaranteed to prevent selection bias. The randomization assignments were stored in sequentially numbered, opaque, sealed envelopes (SNOSE). These envelopes were prepared and held by an independent research coordinator who was not involved in the recruitment or assessment of participants. After a participant’s eligibility was confirmed and baseline data were collected, the recruiter would open the next envelope in sequence to determine the participant’s group assignment.

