### Sample size

2.4

The sample size was calculated *a priori* using G*Power software (version 3.1.9.7) for a two-tailed independent-samples t-test. The primary outcome was the difference in the Adherence to Refills and Medications Scale (ARMS-7) score between the intervention and control groups at the end of the study period. The following parameters were used for the calculation: Significance Level (*α*): A two-tailed α of 0.05 was considered statistically significant. Statistical Power (1-*β*): The desired power (1-β) was set at 0.80. Effect Size (Cohen’s d): Based on a review of similar literature (65, 66), we hypothesised a mean ARMS-7 score of 10.0 (SD = 2.0) in the control group and 9.0 (SD = 2.0) in the intervention group. This corresponds to a mean difference of 1.0 and a pooled standard deviation of 2.0, yielding a medium effect size (Cohen’s d) of 0.5. The sample size was calculated using the following formula:

$$n={\left(\frac{Z_{\alpha /2}+Z_{\beta }}{\Delta /\sigma }\right)}^{2}$$

Using these parameters (*α* = 0.05, power = 0.80, effect size d = 0.5), the required sample size was determined to be 32 participants per group.

To compensate for potential participant dropouts and ensure adequate power for the final analysis, we inflated the sample size by an estimated attrition rate of 20%. This resulted in a final target recruitment of 40 participants per group, for a total sample size of 80 stroke patients.

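### The named between-arm tests adjust for neither baseline ARMS-7 nor the NIHSS randomisation stratum; they are valid but give up precision, and the within-arm tests do not address the treatment effect

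*Protocol article*

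**What the plan says.** **Randomisation.** Section 2.2 states that "the randomization was stratified by baseline NIHSS score", in two levels (5 or below, above 5), with fixed blocks of 4 and 1:1 allocation. The stated purpose is to control imbalance in prognostic factors.

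**Outcome.** Section 3 defines the primary outcome as change in medication adherence from baseline, at 3 and 6 months. Table 2 in section 4 has ARMS-7 collected at 0, 3 and 6 months.

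**Sizing.** Section 2.4 sizes the trial "for a two-tailed independent-samples t-test" on the ARMS-7 difference at the end of the study, with a "mean difference of 1.0 and a pooled standard deviation of 2.0". It arrives at 32 per group, or 40 after 20% attrition.

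**Analysis.** Section 5.10 says that "independent samples t-tests or one-way ANOVA were employed for data conforming to a normal distribution", with Mann–Whitney or Kruskal–Wallis tests otherwise. It continues: "Paired t-test was used for intra-group comparisons, and repeated-measures ANOVA was used to evaluate the trend of changes in each index". For participants lost to follow-up, "we will use multiple imputation to handle missing outcome data". It names no covariate and marks no test as the primary one. Section 6.1 adds that a statistical expert will be consulted on the choice of method.

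**The concern.** Two variables that could sharpen the comparison are already in hand, and no named test adjusts for either. One is baseline ARMS-7, usually the strongest predictor of later ARMS-7. The other is the NIHSS stratum, which the design itself treats as prognostic. An analysis should normally reflect the restriction placed on the randomisation; if it does not, the standard error fails to credit the balance that stratification bought.

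The repeated-measures ANOVA brings a further problem. With baseline entered as one of three outcome visits, its group main effect averages in a visit at which no treatment effect can exist. The within-arm paired t-tests compare each arm with its own past, so they say nothing about the difference between arms. Unless they are labelled descriptive, a significant change in one arm and not in the other invites a false reading.

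At stake is power in a small trial, and a clear answer to which result counts as the primary comparison.

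**Working it through.** **Inputs from section 2.4.** "A two-tailed α of 0.05 was considered statistically significant"; "The desired power (1-β) was set at 0.80"; difference 1.0; SD 2.0; 32 evaluable per arm.

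**Assumptions, not in the document.** The correlation ρ between baseline and follow-up ARMS-7 is taken as 0.3, 0.5 or 0.7. The share R² of ARMS-7 variance explained by the NIHSS stratum is taken as 5% to 20%. The repeated-measures figures assume equal correlation between visits and an effect of 1.0 at both 3 and 6 months.

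**Step 1: the plan's own figure.** The printed formula gives (1.960 + 0.842)² / 0.5² = 31.4, so 32; and 32 / 0.8 = 40. The figure can be traced, but the formula lacks the factor 2 needed to compare two groups. With it, 2 × 31.4 = 62.8, so 63 per group (64 by exact t). That is a separate fault. It matters here because 32 per arm gives the unadjusted t-test a power of only 0.504 (exact noncentral t, d = 0.5).

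**Step 2: power at 32 per arm under each reading.**
- End-of-study t-test: SD 2.0, standard error 2.0 × √(2/32) = 0.500.
- Change-score t-test: SD = 2√(2(1 − ρ)) = 2.37, 2.00, 1.55.
- Baseline-adjusted (ANCOVA): SD = 2√(1 − ρ²) = 1.91, 1.73, 1.43; standard errors 0.477, 0.433, 0.357.
- Repeated-measures group main effect: the difference shrinks to (0 + 1 + 1)/3 = 0.667, with SD of the three-visit mean 2√((1 + 2ρ)/3) = 1.46, 1.63, 1.79.

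| Analysis | ρ = 0.3 | ρ = 0.5 | ρ = 0.7 |
|---|---|---|---|
| Unadjusted t-test at 6 months | 50% | 50% | 50% |
| Change-score t-test | 38% | 50% | 72% |
| Repeated-measures, group main effect (simulated) | 42% | 35% | 30% |
| Repeated-measures, group-by-time (simulated) | 38% | 51% | 75% |
| Baseline-adjusted | 54% | 62% | 79% |

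The t-test, change-score and adjusted rows are exact noncentral-t values. The repeated-measures rows come from 4,000 simulated trials per setting, with stratified blocks of 4 and R² = 5%. A closed-form check of the main effect gives 44%, 36% and 31%. In the same simulations ANCOVA with baseline and stratum had 53%, 61% and 78%.

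**Step 3: size needed with adjustment.** Multiplying 62.8 by (1 − ρ²) gives 57.1, 47.1 and 32.02, so 58, 48 and 33 per arm for 80% power. Only at ρ of about 0.7 or higher does the planned 32 come close.

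**Step 4: leaving out the stratum.** With strata balanced across arms, the true variance of the arm difference is (1 − R²) times what the t-test estimates. The rejection rate under no effect is then about 2[1 − Φ(1.96/√(1 − R²))]: 4.4% at R² = 5%, 3.9% at 10% and 2.8% at 20%. Simulation with balanced strata gave 3.8% at 10% and 2.7% at 20%. Simulation with randomly filled blocks gave 4.3% to 5.0% at R² = 5% and 3.9% at 15%; adjusted for baseline and stratum, the rate was 4.7% to 5.2%. The error is therefore in the conservative direction throughout.

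**Step 5: within-arm tests.** Suppose there is no arm difference and both arms improve by 0.7 points, with ρ = 0.5. The SD of change is 2.0, and each arm's paired t-test is significant about half the time (probability p). One arm is then significant and the other not with probability 2p(1 − p), about 0.50. The simulation gave 50%.

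**The case against.** The strongest reply is that nothing here is invalid. Randomisation makes the unadjusted t-test a fair test, and section 6.1 leaves room for expert advice. A condensed article may also leave covariates to an analysis plan that is not shown. The first part stands, and the point is therefore one of precision. The last part answers less than it seems to: section 5.10 does not stay silent on method but lists particular tests, and the point is about those.

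Three stronger readings are tempting, and the document does not support them.

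- **That the error bars are wrong in a way that produces false positives.** Omitting baseline widens the interval but leaves it valid. Omitting the stratum makes it slightly too wide. How much depends on an R² and a split between strata that the document does not give; the eligibility criteria (able to use a smartphone, no impaired consciousness) make an even split doubtful.
- **That baseline ARMS-7 is ignored altogether.** Repeated-measures ANOVA and paired t-tests both use the baseline visit as data; what is missing is its use as a covariate. Section 5.10 ties the ANOVA to trend, which points to the group-by-time term. At ρ = 0.7 that term trails ANCOVA by only a few points (75% against 78%), so the main-effect figures alone would overstate the loss.
- **That anyone with a missed visit is dropped.** The planned multiple imputation answers this. What remains is practical: an estimate with its standard error pools directly across imputed datasets, and a repeated-measures F or a Mann–Whitney U does not.

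The wording of section 5.10 also leaves it possible that the t-tests are preliminary univariate checks. That uncertainty supports naming a primary analysis. Finally, the paired tests are not called evidence of effect, so the risk lies in how they may later be read.

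**Conclusion.** The point holds as a loss of precision and of clarity, and not as a validity failure. In the calculations above, baseline adjustment has more power than each of the stated tests at every correlation considered. Against the unadjusted t-test at 32 per arm the gain is about 4, 12 or 28 percentage points for ρ of 0.3, 0.5 or 0.7 (50% to 54%, 62% or 79%). Against the group-by-time test it is wide at low correlation and small at high correlation.

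Omitting the NIHSS stratum lowers the t-test's type I error to about 4.5% to 2.7%, for an assumed 5% to 20% of variance explained and balanced strata. Within-arm paired t-tests cannot support a claim of treatment effect.

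All gains rest on an assumed ρ. Adjustment is not a repair for the sample-size formula: 80% power at 32 per arm needs ρ of about 0.7 or higher.

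**What to change.** In section 5.10, name one primary between-arm estimate: the ARMS-7 difference at 6 months, the end of the study, adjusted for baseline ARMS-7 and NIHSS stratum, with a 95% confidence interval. Either ANCOVA at 6 months or a linear mixed model on the 3- and 6-month values will do; in both, baseline is a covariate and not an outcome visit. Each yields an estimate with a standard error, so it fits the planned multiple imputation.

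Use the same model for the other continuous scales. Fix the primary method in advance so that a normality check does not choose it; a rank-based analysis can serve as a sensitivity analysis. Label the within-arm paired t-tests descriptive only.

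The cost is a rewritten paragraph. Both covariates are already collected, SPSS is already the planned software, and no visit or measurement is added. The sample size in section 2.4 needs its own correction.

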## Study management

6

### Data collection

6.1

Prior to the formal commencement of the study, all investigators will receive systematic training and pass a competency assessment to ensure accuracy and consistency of data collection. The investigators are responsible for recording all clinical observations and laboratory test results in detail on a pre-designed subject registration form, this includes accurate registration and coding of the study subjects to minimise the dropout rate during the follow-up period. In order to maintain data comparability between the intervention and control groups, the time points of the survey and questionnaire content will be designed to be essentially the same. The researcher will ensure that each section of the registration form is completed correctly, and each completed submission will need to be dated and signed in order to validate and retrospectively trace the data at the end of the study. During the data analysis phase, a double-checking mechanism will be implemented to improve the accuracy of data entry. In addition, the research team will consult a statistical expert to select the most appropriate statistical method for analysis.

### Storage and archiving of data

6.2

Investigators are required to archive all trial data, including lists of subject identification codes, source data and investigator documentation, and records of related correspondence in a study-specific database. All source data and related documents of the study will be archived after the completion of the trial in accordance with legal and regulatory requirements to ensure long-term preservation and traceability of the data.

### Ethics and regulations

6.3

All procedures of this trial, including conduct, evaluation and documentation, will follow the ethical principles set out in the Good Clinical Practice (GCP) for pharmaceutical clinical trials and the Declaration of Helsinki. The trial will be conducted in strict accordance with local laws and regulations and the protocol has been approved by the Ethics Committee of the Linyi City Central Hospital in Shandong Province (LCH-LW-2025031).

### Ethics committee

6.4

To ensure the quality of the study, the trial will report the progress of the study to the Ethics Committee on a regular basis and submit revised protocols for approval when necessary. The Ethics Committee has the right to request suspension or termination of the trial if any problem arises during the study.

### Informed consent

6.5

All participants will voluntarily sign an informed consent form after fully understanding the purpose, methods, potential risks and benefits of the study. For patients who are unable to sign the informed consent form, the option of verbal consent will be offered and it will be ensured that they understand the study and agree to participate.

### Confidentiality

6.6

Patients’ personal information will be strictly protected and used only for research purposes. The research team will take the necessary steps to ensure data security, including the use of encryption and limiting data access.

### Investigator responsibilities

6.7

The study leader will oversee the entire study process and ensure that all investigators comply with the trial protocol and study standards. Investigators are required to ensure the authenticity and integrity of the data and maintain high professional and ethical standards during the study.

### Approval of trial protocol and revisions

6.8

Any revisions to the trial protocol must be reviewed by the study leader and approved by the ethics committee before implementation. The investigator will document all revisions and ensure that all team members are aware of and follow the updated trial protocol.

### Data monitoring

6.9

The Data Monitoring Committee (DMC) will consist of at least two experts independent of the study team who will regularly monitor the study data, assess the validity and safety of the study and report to the Ethics Committee. The DMC will have the authority to recommend the suspension or termination of the trial if it finds that the study is deviating from the approved protocol or if there are problems.

### Safety

6.10

All serious adverse events (SAEs) and adverse events (AEs) reported by patients or detected by investigators during the study will be recorded and monitored. All SAEs and AEs must be reported to the Principal Study Leader within 24 h of their occurrence and notified to the Monitor and Ethics Committee in accordance with established procedures. The study leader will be responsible for ensuring that all SAEs and AEs are fully documented and that appropriate measures are taken to protect patient safety and rights. Given that digital interventions may present unique challenges, we systematically monitored unintended consequences at the non-clinical level, including: difficulties or frustrations encountered when using the AI-HEALS platform (such as navigation issues, slow loading times, or unclear operational guidance); increased anxiety, stress, or feelings of being overwhelmed stemming from the educational content or the technical use itself; any evidence suggesting patients misunderstood educational information or used the system in unintended ways, which could lead to confusion or erroneous health behaviors. To capture these effects, research assistants proactively telephoned intervention group participants weekly to enquire about any technical difficulties or negative emotions they might have encountered. Participants were encouraged to report any adverse experiences via the research helpline at any time. All reported unintended consequences were documented, with the research team conducting weekly reviews to identify patterns and implement timely solutions. This enabled the provision of additional technical support to patients or clarification of educational content.

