**Methods:**

The study will conduct a single-blind, single-centre randomised controlled trial in Linyi City Central Hospital, Shandong Province, with IS patients over 18 years old. The intervention group will receive routine care combined with the AI-HEALS, while the control group will receive routine care alone. Primary outcomes include changes in medication adherence levels at baseline and 1, 3, and 6 months of follow-up. Secondary outcomes encompass medication behavior management, medication literacy, self-efficacy, social cognition, psychological levels, and clinical outcome indicators.

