### Study design

2.1

This study is a hospital-based randomised controlled trial designed to compare the effectiveness of an intervention based on the AI-HEALS’s theory of protective motivation combined with drug literacy education with a usual care control group. The study will use quantitative methods, measured by clinical reagent tests and internationally used scales to ensure the objectivity of the trial. The study period is scheduled from June to December 2025. The control group will receive standard care, including admission education, dietary and psychological care, medication and rehabilitation care, life care, health counselling, and prognostic guidance. The intervention group will receive the AI-HEALS intervention for 3 months on the same basis. Patients will undergo questionnaires and physical examination at baseline, 3 months and 6 months post-intervention to assess changes in self medication behavior management, social cognitive and psychological indices as well as clinical health indice. The flow of the study is shown in Figure 2 and Table 1.

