**Figure 3 fig3:**
[figure not shown]
Schematic diagram of the operation of the intervention system.

The intervention comprises a three-stage core educational programme. The first session is delivered within 48 h of admission (approximately 30 min), the second is scheduled 24–48 h prior to discharge (approximately 30 min), and the third involves remote intervention via the AI-HEALS system following discharge (continuing for approximately 3 months). The intervention is delivered using a hybrid model. The initial two in-hospital sessions comprise face-to-face, one-to-one sessions between nurses and patients, utilising mobile educational services provided by the AI-HEALS system. The post-discharge session is delivered remotely via the AI-HEALS mobile application. All neurological nurses responsible for delivering the intervention underwent mandatory standardised training led by the Head Nurse and neurological physicians. This four-hour training covered the research protocol, theoretical foundations of the intervention, and operational protocols for the AI-HEALS system. To ensure intervention fidelity, the Head Nurse conducted weekly randomised spot checks of 10% of sessions via session recordings and direct observation to verify protocol adherence. To consolidate learning outcomes, the AI-HEALS system automatically delivered daily push notifications containing key medication reminders and health alerts to the intervention group for 3 months post-discharge (see Supplementary material).

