
The AI-HEALS in this study is expected to provide significant support for secondary stroke prevention in China, which will reduce the repetitive workload of healthcare professionals through semi-automated education, thus alleviating the pressure on healthcare human resources. According to the China Health Statistics Yearbook, the ratio of neurologists to patients in China may be as low as 1:2,000, especially when high-quality medical resources are mainly concentrated in tertiary hospitals, the AI-HEALS will be expected to be widely promoted in township and village hospitals with its low-cost capital requirements, providing a boost to improve the uneven distribution of medical resources. It is expected to improve medication adherence of relevant patients and reduce stroke recurrence rate, which in turn will reduce family care costs and social health expenditure. Since 2014, China has become one of the countries with the highest direct medical costs for acute ischaemic stroke (82). Therefore, the health economic benefits of this study deserve further in-depth analysis.

The goal of this study was to construct an innovative intervention programme for secondary prevention medication adherence in ischemic stroke patients by integrating the theory of protective motivation with the medication literacy model and with the help of the AI-HEALS. The rationality and validity of the theoretical framework, the precision of the technological platform, and the adaptability of the implementation strategy of this programme will set a new benchmark for behavioral intervention research in chronic diseases. If the results of the trial are positive, it is expected that this disease intervention model will be expanded to other diseases that require long-term medication use, such as coronary heart disease and diabetes mellitus, to promote the application of the ‘motivation-competence’ dual-driven paradigm of health management in a wider range of disease management.

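### Weekly staff calls go to the intervention arm only and are not listed as part of the intervention, so a difference cannot be credited to AI-HEALS itself and adverse-event reports are not comparable between arms

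*Protocol article*

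**What the plan says.** The abstract defines the comparison: "The intervention group will receive routine care combined with the AI-HEALS, while the control group will receive routine care alone". Section 2.1 sets the length: "The intervention group will receive the AI-HEALS intervention for 3 months on the same basis".

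Section 2.5 describes a hybrid programme: two face-to-face nurse sessions in hospital, then a third stage after discharge. On that stage it says: "The post-discharge session is delivered remotely via the AI-HEALS mobile application". It adds automatic daily push messages for 3 months. It does not mention telephone calls by staff.

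The calls appear only in section 6.10, among the measures for monitoring unintended effects of the platform: "research assistants proactively telephoned intervention group participants weekly to enquire about any technical difficulties or negative emotions they might have encountered". The reports were reviewed weekly and acted on: "This enabled the provision of additional technical support to patients or clarification of educational content".

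For general safety, the same section says: "All serious adverse events (SAEs) and adverse events (AEs) reported by patients or detected by investigators during the study will be recorded and monitored". It describes no scheduled enquiry for controls.

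The Discussion expects a system "which will reduce the repetitive workload of healthcare professionals through semi-automated education". Its limitations paragraph concedes possible performance bias, because staff knew the allocation. It then argues that contamination would weaken the observed effect, so that the findings should be read as cautious. It does not mention the calls.

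**The concern.** A call that asks about problems and leads to help is a form of support, whatever section it is described in. One arm gets it weekly and the other does not. Technical help and clarified teaching could plausibly affect medication self-efficacy (SEAMS) and self-reported adherence (ARMS-7). Regular enquiry about low mood or stress touches the same ground as PHQ-4.

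Two things are at stake. The first is attribution: the second objective in the Introduction is to evaluate AI-HEALS itself, on self-efficacy, quality of life and psychological status among other things, and the Discussion looks ahead to inexpensive use in smaller hospitals. A trial that includes weekly calls does not test the system without them. The second is safety reporting: where one arm is asked every week and the other relies on patients coming forward or investigators noticing, more events can be recorded in the first arm at the same true risk.

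**Working it through.** The plan states no figure on this point to reproduce. The check sets the passages side by side, then shows what assumed values would imply.

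**1. Is the contact part of the declared comparison?**

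| Place | Post-discharge human contact, intervention arm | Controls |
|---|---|---|
| Abstract, Methods | none named | none named |
| Section 2.5 | none named; app and push messages | not applicable |
| Section 6.10 | weekly call, with support following from it | no matching call described |

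The calls are part of what intervention patients receive but not of what the plan says is being compared.

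**2. Amount of contact.** The article does not say for how long the calls run. Assuming the 3-month intervention period: 91 / 7 = 13 calls per patient. With the 40 recruited per group in section 2.4, 13 × 40 = 520 calls; with 32 evaluable per group, 13 × 32 = 416.

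**3. Effect on ARMS-7 (illustration).** Inputs from section 2.4: SD 2.0, two-sided α 0.05, 40 per group. The documents give no effect of contact, so a range is assumed. Suppose AI-HEALS has no effect and contact alone improves (lowers) ARMS-7 by c points at the tested time.

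SE = 2.0 × √(2/40) = 0.447

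P(reject) = Φ(c/SE − 1.96) + Φ(−c/SE − 1.96)

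| c (assumed) | c/SE | P(reject), 40 per group | P(reject), 32 per group |
|---|---|---|---|
| 0 | 0 | 5% | 5% |
| 0.2 | 0.45 | 7.3% | 6.9% |
| 0.3 | 0.67 | 10.3% | 9.2% |
| 0.5 | 1.12 | 20.1% | 17.0% |

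For 32 per group, SE = 2.0 × √(2/32) = 0.5. Above c = 0, most of these rejections favour the intervention, the opposite direction from dilution by contamination.

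**4. Effect on event counts (illustration).** Assume the same true risk of 30% in both arms, 40 patients per arm, 90% of events found with calls and a lower share without. Expected count = 40 × 0.30 × share found.

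| Share found in controls (assumed) | Intervention | Control | Apparent risk ratio |
|---|---|---|---|
| 70% | 10.8 | 8.4 | 1.29 |
| 50% | 10.8 | 6.0 | 1.8 |
| 30% | 10.8 | 3.6 | 3.0 |

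These ratios come from detection alone. Tables 3 and 4 show direction and mechanism; they do not estimate this trial's bias.

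**The case against.** Several points on the other side have force.

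- **The calls are not hidden.** Section 6.10 describes them openly, and section 2.5 refers to supplementary material that is not at hand. What stands is narrower: the main description of the intervention and the stated comparison omit them.
- **The programme was never fully automated.** It already includes two nurse sessions, so a pure AI effect was not available anyway. That is correct, and the package effect remains estimable. But weekly contact after discharge is a further component, and it falls in the stage presented as app-delivered.
- **The calls mainly target platform problems,** which have no counterpart in controls, and no between-arm test of harms is stated. The rule on adverse events names no arm, and a helpline exists. So the detection concern is confined to events that both arms can have, such as anxiety, distress and general adverse events mentioned on a call.
- **Controls are not without contact.** Section 2.3 gives each group its own follow-up times. Only the weekly proactive call is one-sided.
- **The workload sentence is an expectation about healthcare professionals,** while the callers are research assistants. It is not a trial outcome, so it needs only a qualification.

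Three stronger readings are tempting but unsupported. A reader might infer that the calls contradict section 6.1. That section promises only that "the time points of the survey and questionnaire content will be designed to be essentially the same", and the calls are not described as a study survey or outcome questionnaire. A reader might infer that readmissions would be found more often in the intervention arm. Section 5.9 defines readmission as unscheduled admission to the trial hospital, with systematic review of all readmissions, and the calls are not said to ask about admissions. A reader might also infer that outcome assessment is unblinded. Section 2.2 says that assessors are blinded and that an independent third party collects data. The article does not say that callers and interviewers are the same people; it only leaves this open, since section 3 has researchers guiding the questionnaires by telephone after discharge.

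**Conclusion.** The concern holds in a limited form. The one-sided calls, and the support that follows from them, are stated in section 6.10 and absent from the declared comparison. The trial can conclude about AI-HEALS together with nurse sessions and weekly staff calls, compared with routine care. It cannot assign a difference in ARMS-7, SEAMS or PHQ-4 to AI-HEALS itself. The Discussion's cautious-estimate statement rests on contamination alone and ignores an influence that can act in the opposite direction. Reports of adverse events, especially anxiety or distress, are not comparable between arms as collected.

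The size of neither effect can be found from the documents. The figure of about 13 calls assumes that they last through the 3 months, and every contact effect, event risk and share of events found used above is an assumption. The conclusion rests on the asymmetry stated in the text, not on those numbers.

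**What to change.** 1. **Name the calls.** List the weekly calls in section 2.5 as part of the tested intervention. Word the conclusion and the workload statement for AI-HEALS with nurse sessions and weekly staff calls. Remove or qualify the statement that the findings are a cautious estimate.
2. **Ask both arms alike.** Use the same adverse-event script in both arms at the existing 3- and 6-month contacts, and base any between-arm comparison of adverse events on those reports. Report all other events in full by method of detection, with platform-specific problems shown for the intervention arm only. No event leaves the safety record. Leave the readmission outcome as section 5.9 defines it.
3. **Separate the roles.** State that the callers do not administer the telephone outcome questionnaires, so that the blinding in section 2.2 can hold.

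The cost is wording in sections 2.2, 2.5, 6.10 and 7, a short script at contacts that already take place, and some care in assigning staff. The downside is a narrower claim, with some events shown outside the between-arm comparison.
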